## Abstract

**Background:**

According to international guidelines, the goal of asthma management is to achieve and maintain control of the disease, which can be assessed using composite measures. Prospective studies are required to determine how these measures are associated with asthma outcomes and/or future risk. The ‘*InternationaL cross-sectIonAl and longItudinal assessment on aSthma cONtrol (LIAISON)*’ observational study has been designed to evaluate asthma control and its determinants, including components of asthma management.

**Methods/design:**

The LIAISON study will be conducted in 12 European countries and comprises a cross-sectional phase and a 12-month prospective phase. Both phases will aim at assessing asthma control (six-item Asthma Control Questionnaire, ACQ), asthma-related quality of life (Mini Asthma Quality of Life Questionnaire, Mini-AQLQ), risk of non-adherence to treatment (four-item Morisky Medication Adherence Scale, MMAS-4), potential reasons for poor control, treatment strategies and associated healthcare costs.

The cross-sectional phase will recruit > 8,000 adult patients diagnosed with asthma for at least 6 months and receiving the same asthma treatment in the 4 weeks before enrolment.

The prospective phase will include all patients with uncontrolled/poorly controlled asthma at the initial visit to assess the proportion reaching control during follow-up and to examine predictors of future risk. Visits will take place after 3, 6 and 12 months.

**Discussion:**

The LIAISON study will provide important information on the prevalence of asthma control and on the quality of life in a broad spectrum of real-life patient populations from different European countries and will also contribute to evaluate differences in management strategies and their impact on healthcare costs over 12 months of observation.

**Trial registration:**

ClinicalTrials.gov identifier, NCT01567280.

## Background

Asthma is a serious global health problem with an increasing prevalence worldwide. People of all ages are affected by this chronic airways disorder that, when uncontrolled, can place severe limits on daily life and is sometimes life threatening or even fatal [1]. A consensus recently stated that there are 300-million people suffering asthma worldwide [2]. Very recently, the costs of persistent asthma have been estimated as EURO 19.3-billion in the whole European population aged from 15 to 64 years, with a mean total cost per patient ranging from EURO 509 in controlled asthma up to EURO 2,281 in uncontrolled asthma [3].

Asthma control is a central focus of the Global Initiative for Asthma (GINA) Guidelines [1], in which clinicians are encouraged to concentrate on its assessment based on the clinical manifestations of disease: symptoms, lung function and the presence or history of exacerbations [4]. Since 2006, GINA guidelines recommend to classify patients into controlled, partly controlled and uncontrolled asthmatics, and highlight that the best way to achieve asthma control is through inhaled anti-inflammatory therapy, monitoring and asthma education [1]. The assessment of asthma control should include not only control of the clinical manifestations but also control of the expected future risk to the patient such as exacerbations, accelerated lung-function decline and side effects of treatments [1].

Treatment of asthma should aim at achieving and maintaining disease control for prolonged periods with a minimum amount of medications, with due regard to the tolerability of treatment, potential for adverse effects, and costs. Effective therapies are now available, and allow attaining asthma control in the majority of patients in randomised controlled trials [5].

However, the proportion of patients lacking asthma control remains high in both adults and children, reflecting a significant gap between what treatments can achieve and the real-life situation [6-10], even in patients receiving regular treatment with inhaled corticosteroids [11,12].

Well-validated self-assessment questionnaires have been developed to monitor the level of asthma control, such as the Asthma Control Questionnaire (ACQ) [13] and the Asthma Control Test (ACT) [14]. These instruments measure asthma symptoms, limitation of activities and need for rescue medication, and have been used in most of the recently published surveys on asthma control.

Country-specific or multinational studies based on the ACQ or the ACT have shown an uneven situation of the asthma control in Europe. In a recent study carried out in the Netherlands [15], the percentage of patients with partly controlled or uncontrolled asthma evaluated with the ACQ was 35.5% and 27.0%, respectively. In another study performed in five European countries [16], approximately half of asthmatic subjects were not well controlled according to the ACT score, and no substantial improvement was found in a more recent survey conducted in the same countries [17]. Conversely, a recent observational study carried out in Italy [18] showed that only 15.8% and 19.8% of patients referred to respiratory medicine centres had partly controlled or uncontrolled asthma, respectively, based on the ACT score. These results confirm previous evidence from a survey conducted in Italy showing that 64.7% of patients with asthma are well controlled [19].

Other studies have evaluated the level of asthma control using different methods of assessment, such as patients’ perception of symptoms [6,20], a questionnaire based on asthma symptoms and recent history [21], and the GINA classification of controlled, partly controlled and uncontrolled asthma [12]. Overall, the results of these studies indicated a suboptimal level of asthma control and variability in the prevalence of controlled patients among European countries [12] or worldwide macro-areas [6].

Most of the observational studies performed until now comprised relatively small populations unrepresentative of the asthmatic population of the countries in which they were performed. In addition, they were mainly based on a cross-sectional design, which does not allow assessing the level of asthma control over time and the impact of adherence to treatment. Furthermore, the limitations due to heterogeneity among methods for assessment of asthma control such as telephone interviews, web-based questionnaires or postal questionnaires, do not allow reaching firm conclusions on patients’ attitudes to asthma management, adherence, level of asthma control and its impact on patients’ quality of life in Europe. The identification of major reasons for a suboptimal asthma control can help the physician to optimise asthma management and the patient to improve his/her perception of the disease.

Based on this background, the ‘*InternationaL cross-sectIonAl and longItudinal assessment on aSthma cONtrol (LIAISON)*’ study has been designed to include a cross-sectional phase and a 12-month prospective phase in order to estimate the level of asthma control in real life, its determinants and its changes during a 1-year follow up.

## Objectives

Table 1 summarises the primary and secondary objectives of the study. The primary objectives of the cross-sectional phase are to evaluate the proportions of patients with controlled, partly controlled and uncontrolled asthma, and to assess the health-related quality of life and the factors associated with asthma control in a real-life population of asthmatic patients.

**Table 1 T1:** Primary and secondary objectives to be investigated

	**Cross-sectional phase**	**Longitudinal phase**
**Primary objectives**	• Prevalence of patients with controlled or uncontrolled/partly controlled asthma	• Proportions of patients with controlled, partly controlled and uncontrolled asthma after 12 months from the cross-sectional phase visit
	• Health-related quality of life	• Proportion of patients with uncontrolled/partly controlled asthma switching to controlled asthma after 12 months from the cross-sectional phase visit
	• Factors associated with asthma control	• Changes in quality of life after 12 months
		• Factors associated with the gain of asthma control
**Secondary objectives**	• Proportion of asthmatic smokers and their level of asthma control	• Association between (current) level of asthma control and (future) risk of exacerbations
	• Antiasthmatic therapies	• Relation between change in asthma control and change in rate of exacerbations during the longitudinal phase (including stratified analyses according to GINA treatment level)
	• Medication adherence	• Antiasthmatic therapies
	• Healthcare costs over 3 months before the cross-sectional phase visit	• Proportion of patients with uncontrolled/partly controlled asthma that reach control after 3 and 6 months from cross-sectional phase visit
	• Rate of severe exacerbations in the last 12 months before the cross-sectional phase visit	• Medication adherence
	• Reasons for poor control according to the Investigators’ and the patients’ opinion	• Healthcare costs
	• Lung function parameters, if available	• Rate of severe exacerbations and the time to first severe exacerbation
		• Reasons for poor control according to the Investigators’ and the patients’ opinion
		• Lung function parameters, if available

The primary objectives of the prospective phase (which will include only patients with uncontrolled and partly controlled asthma classified according to the six-item ACQ score) are to evaluate the proportions of uncontrolled/partly controlled patients reaching asthma control after 12 months from the cross-sectional phase visit, to assess the health-related quality of life and the factors associated with gain of asthma control as well as predictors of those who are at future risk of exacerbations.

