#### Six-item asthma control questionnaire (ACQ)

The six-item ACQ [13] includes a measure of the top five asthma symptoms (woken at night by symptoms, day-time symptoms, limitation of daily activities, shortness of breath and wheeze) and the use of quick-relief bronchodilators. The asthma control level will be evaluated according to the following thresholds: controlled asthma: ACQ score ≤ 0.75; partly controlled asthma: 0.75 < ACQ score <1.5; uncontrolled asthma: ACQ score ≥ 1.5.

As long as many factors are to be considered when a symptom-based approach is being used to achieve optimal disease control [22]*,* the possible reasons for poor control (e.g. comorbidities, seasonal worsening, depression, etc.) will be collected both according to the doctors’ and patients’ opinions using a multiple choice system from a drop down list.

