### Statistical analysis

All recorded variables will be tabulated using summary statistics for continuous variables and frequency tables (absolute and relative) for categorical variables. All outcomes will be stratified by country.

Logistic regression analysis will be used to analyse binary variables (e.g. the association between the asthma control level and quality of life in the cross-sectional phase). Models will include confounding factors if identified by the exploratory analysis. As measures of association between the response variable (e.g. the asthma control level) and the independent variables, the odds ratios (ORs) with the relative 95% CI along with the p-value will be reported. For continuous variables, the estimated OR will be expressed for a change of *c* units in the covariate.

The analyses of the results of the longitudinal phase will be conducted using mixed-effect models (SAS Proc MIXED) to estimate the means of the changes in the scores over time from the cross-sectional phase visit.

The healthcare costs will be evaluated by descriptive analysis, considering the time frames of 3 months before the cross-sectional phase visit and the longitudinal phase period.

The number of severe exacerbations in the last 12 months before the cross-sectional phase visit and the number of severe exacerbations per patient/year at each visit will be descriptively analysed overall and by level of asthma control. The rate of severe exacerbations per patient/year will be calculated as the total number of experienced severe exacerbations over the longitudinal phase on total number of days of observation of patients at risk. The time to first asthma severe exacerbation during the longitudinal phase will be analysed with the Kaplan-Meier survival analysis, and their significance by the log-rank test. Predictors of exacerbations will be analysed by means of a multivariate logistic model. A stepwise selection approach will be used to identify the most significant prognostic factors and to eliminate the unimportant ones. Using this methodology, a final predictive model containing just the important variables will be created.

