## Discussion

The aim of the LIAISON study is to estimate the level of asthma control and quality of life in a European real-life setting and their evolution during 1 year, using validated self-administered tools such as the six-item ACQ and Mini-AQLQ. Further objectives are: to evaluate the reasons for lack of asthma control, the medication adherence, the impact of pharmacological treatment, the number of severe exacerbations and healthcare resources use.

Several real-life asthma studies have been reported elsewhere but the variability in patients’ samples due to current treatments, the geographical location and the criteria for exclusion from study participation has led to different outcomes in terms of prevalence of asthma control. Moreover, it is difficult to compare the results of these studies due to the different methods used in data collection, which included patient self- or web-administered questionnaires, office-based or hospital-based physician consultations [18].

With the inclusion of more than 8,000 patients in the cross-sectional phase and of more than 4,000 in the longitudinal phase of the study, the LIAISON study will be the largest naturalistic study ever performed in 12 European countries to investigate asthma control and the impact of asthma control on quality of life and future risk of exacerbations. Furthermore, the longitudinal phase of the study will provide important information on the adequacy and effects of management strategies implemented in each country to reach control in the following year.

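### Month-12 gain of control pools partly controlled and uncontrolled starters and is split only by country, yet country results are to be read as evidence on management with no commitment to account for entry ACQ

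*Protocol article*

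**What the plan says.** Table 1 of the protocol article (Objectives) lists as a primary longitudinal objective "Proportion of patients with uncontrolled/partly controlled asthma switching to controlled asthma after 12 months from the cross-sectional phase visit". The text below the table and the Sample size section pool the same two groups.

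The ACQ section sets the classes: "controlled asthma: ACQ score ≤ 0.75; partly controlled asthma: 0.75 < ACQ score <1.5; uncontrolled asthma: ACQ score ≥ 1.5".

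The Statistical analysis section states "All outcomes will be stratified by country". It adds a description by level of asthma control for severe exacerbations, but names no such breakdown for gain of control. On covariates it says "Models will include confounding factors if identified by the exploratory analysis". Baseline ACQ is neither named nor ruled out. A further primary objective is "Factors associated with the gain of asthma control".

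The Discussion says the longitudinal phase will give "important information on the adequacy and effects of management strategies implemented in each country to reach control in the following year". It also calls country-specific analyses reliable and expects the study to evaluate differences in care among countries.

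**The concern.** The outcome is a threshold crossing, and the two groups in its denominator start at different distances from the threshold. A patient entering at ACQ 0.9 needs a fall of 0.15; one entering at 2.0 needs a fall of 1.25. The proportion reaching control therefore depends on who was enrolled as well as on what was done for them.

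For one overall description this does no harm. It matters once the proportion is set out country by country and read as a sign of how adequate each country's management is. A country whose non-controlled patients are mostly partly controlled will look better than one whose patients are mostly uncontrolled, even if care is the same. The Background and Discussion themselves report wide variation in control between countries, so unequal entry mixes are to be expected.

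**Working it through.** **1. The plan's own figures (Sample size section).**
- Not controlled at entry: 8,150 × (1 − 0.375) = 5,093.75, stated as 5,094.
- Evaluable at month 12: 5,093.75 × 0.80 = 4,075, as stated.
- Half-width: 1.96 × √(0.45 × 0.55 / 4,075) = 1.53 points, stated as ±1.5%.

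All three reproduce.

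**2. Entry mixes (Background).**
- Dutch study, ACQ: 35.5% partly controlled and 27.0% uncontrolled. Share partly controlled among the non-controlled: 35.5 / 62.5 = 56.8%.
- Italian study, ACT, patients referred to respiratory centres: 15.8% and 19.8%. Share: 15.8 / 35.6 = 44.4%.
- Difference in share: 12.4 percentage points.

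**3. Class-specific chance of reaching control (assumed model).** The article gives no class-specific rates. Assume normal entry ACQ matching the 37.5 / 35.5 / 27.0% split. With z(0.375) = −0.319 and z(0.73) = 0.613:
- SD = (1.5 − 0.75) / (0.613 + 0.319) = 0.805
- mean = 0.75 + 0.319 × 0.805 = 1.007

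Assume further that entry and month-12 scores are bivariate normal with correlation ρ, and set the month-12 cut so that 45% of those with entry ACQ above 0.75 are controlled. The last column is the gap × 0.124, the country difference under identical care.

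| ρ (assumed) | Partly controlled starters | Uncontrolled starters | Gap (points) | Country difference (points) |
|---|---|---|---|---|
| 0.4 | 52.8% | 34.7% | 18.1 | 2.2 |
| 0.6 | 57.7% | 28.3% | 29.4 | 3.7 |
| 0.8 | 64.7% | 19.1% | 45.6 | 5.7 |

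Check at ρ = 0.6: 0.568 × 57.7 + 0.432 × 28.3 = 45.0%. More generally, each 10-point difference in the share partly controlled moves the country result by 1.8 to 4.6 points.

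**4. Sampling error per country.**
- Minimum enrolment: 400 × 0.625 × 0.80 = 200 evaluable; 1.96 × √(0.2475 / 200) = ±6.9 points. Difference of two such countries: × √2 = ±9.8.
- Average enrolment: 8,150 / 12 = 679, about 340 evaluable; ±5.3 points. Difference of two: ±7.5.

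**5. Precision if reported by entry class.**
- Partly controlled: 4,075 × 0.568 = 2,315; 1.96 × √(0.2475 / 2,315) = ±2.0 points.
- Uncontrolled: 4,075 × 0.432 = 1,760; ±2.3 points at a rate of 45%, ±2.2 at 34.7% and ±1.8 at 19.1%.

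**The case against.** The strongest reply has four parts.

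- **No formal country comparison is planned.** A reader might infer that countries will be compared on gain of control with baseline ACQ left out. The article does not say that: it specifies stratified output, no between-country test, model or ranking, and does not exclude baseline ACQ. This stands. What remains is the Discussion's reading of the country results, which the stratified proportions cannot support alone.
- **Pooling is a legitimate choice.** A reader might infer that the 45% target is wrong. It is not: the proportion of all non-controlled patients who reach control is a valid descriptive quantity, and its precision is correctly computed. This stands in full.
- **An exploratory step would pick up baseline control anyway.** With 2,315 and 1,760 patients, the class differences above have z of about 12 to 33, so if baseline is screened it could hardly be missed. This largely stands for the logistic model. It does not reach the country-stratified proportions, which are not model output. A covariate known in advance to fix the distance to the cut-off also need not depend on a screen.
- **The size is assumed, and tables and covariate lists belong in an analysis plan.** The correlation is assumed, and the two mixes come from different instruments and settings. The 2 to 6 points are smaller than a two-country sampling error, and the pooled ±1.5 is not the right yardstick for them. All this stands, and an analysis plan that is not shown may already adjust. But the article itself states both the breakdown by country and the interpretation, and these do not fit together as written.

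**Conclusion.** The point holds in a limited form. The article commits to a country breakdown of a pooled threshold outcome and reads country results as evidence on management, without committing to report by entry class or to adjust for entry ACQ. Crude country proportions are then confounded by entry severity.

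The direction follows from the article's cut-offs together with any positive correlation between entry and month-12 scores. The size, about 2 to 6 points, rests on the assumed normal model, a correlation of 0.4 to 0.8 and the illustrative mixes of 57% and 44%. It is below the sampling error of a single two-country comparison, but it is a bias: it favours countries with milder starters, and enrolling more patients does not reduce it. The overall estimate and the sample size calculation are unaffected.

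**What to change.** In the Statistical analysis section, with a matching line in Table 1:

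1. Report month-12 control class by baseline class (partly controlled, uncontrolled), overall and by country, alongside the pooled proportion.
2. Always include baseline ACQ score in the gain-of-control logistic model, and leave exploratory selection for the other covariates.
3. Before any country difference is read as a difference in management, adjust for baseline ACQ score or standardise to the pooled baseline ACQ distribution. Using the score also handles differences within a class.
4. State the class-specific precision: about ±2.0 points for some 2,315 partly controlled patients, and ±1.8 to ±2.3 points for some 1,760 uncontrolled patients, depending on the true rate.

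If the analysis plan already does this, a sentence in the article is enough. No new data are needed. The cost is a few extra tables and somewhat wider intervals than the pooled ±1.5 points.

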## Methods/design

### Study design

Figure 1 shows the design of the cross-sectional phase and the prospective phase of the study. Subjects satisfying entry criteria will be evaluated in the cross-sectional phase of the study. Asthmatic patients with uncontrolled/partly controlled asthma will be followed for the 12-month prospective phase. Follow-up visits will take place approximately 3, 6 and 12 months after the cross-sectional phase visit.

**Figure 1 F1:**
[figure not shown]
Study design.

### Study population

The study population will include approximately 8,150 patients attending about 160 outpatient hospitals or General Practice clinics distributed across 12 European countries (Austria, Belgium, France, Germany, Greece, Hungary, Italy, the Netherlands, Poland, Spain, Turkey and the United Kingdom). At least 400 patients in about eight centres will be enrolled in each participating country. Consecutive patients visiting the centre during the estimated 12-month recruitment period will be enrolled.

Male and female adult (aged ≥18 years) patients with a clinical diagnosis of asthma (according to GINA guidelines and confirmed by a chest physician) for at least 6 months, and receiving the same antiasthmatic drugs in the last 4 weeks before enrolment, will be eligible for study participation after signing the informed consent.

Patients participating in a clinical trial within the previous 4 weeks or patients suffering from conditions and illnesses that might interfere with the study purpose, according to the investigator’s evaluation, will be excluded from the study.

